#### Training of Researchers and Clinicians at Study Sites

To enable reliable administration of study measures, and to maximize study participation and promote a research culture in study sites, researchers and participating site clinicians will be provided with training in and support for participant recruitment, and administration and clinical application of all study measures. This will include 1-day training in administration of the study narrative interview, incorporating an introductory explanation of the coding system and discussing clinical implications of different types of responses, facilitated by an expert in the interview who developed the coding system (third author). Regular face-to-face site meetings and/or videoconferencing will be held to monitor the study procedures and recruitment progress, and to address implementation challenges. All participating clinicians must be trained and certified to deliver the COS-P intervention prior to their participation in this study.

### Intervention

At all study sites, COS-P will be facilitated to groups of parents according to the original program manual (6) utilizing the associated DVD, over 8 weekly 90 to 120-min sessions; one manual chapter (with associated DVD content) to be completed *per session*. Following standard COS-P research practice, intervention completion will be defined as attendance at a minimum of six sessions ([name] MD, Research Liaison and Medical Director—Circle of Security International, personal communication, 15 August 2017).

To maximize intervention fidelity, collaborating study sites have been chosen, in part, for their adherence to the COS-P manual in their routine delivery of COS-P. Beyond this, as the study aims to evaluate COS-P-as-delivered, intervention fidelity will be assessed by the research team, through post-group interviews with each COS-P facilitator (see interview details below).

### Measures

Study measures were selected for minimum participant burden to ensure feasibility for high-volume outpatient community health settings, and based on their suitability across a broad child age range, their alignment with aspects of parenting targeted by the intervention, and existing evidence of validity, reliability and utility for both research and clinical work.

#### Primary Outcomes

Primary outcomes are caregiving representations, assessed through a self-report questionnaire and a narrative interview, and caregivers' parental mentalization, assessed through a self-report questionnaire, and from caregiver language during a narrative interview and observed caregiver-child interaction.

##### Composite caregiving questionnaire

The CCQ was developed to evaluate primary COS-P outcomes; specifically, components of caregivers' self-reported caregiving representations and parental mentalization. With a view to keeping the questionnaire brief and minimizing repetition, subscales from several validated questionnaires were combined, with their authors' permission. The original rating scales were retained for each subscale. In prior research using the original measures, subscale totals have commonly been reported in addition to (and sometimes, instead of) overall totals. Following initial development, three study sites (sites 1, 2, and 3) piloted the CCQ with COS-P group participants. Feedback from participants, clinicians and service managers led to wording refinements including replacement of “mother” or “parent” with “caregiver,” and providing simpler explanations for some words and phrases that may be unfamiliar to non-native-English speakers. The final study version of the CCQ has 43 items, incorporating:

12 items from two subscales of the tool to Measure Parenting Self-Efficacy (TOPSE)^1^ (49), scored on a 10-point scale, exploring:
– empathy and understanding (six items; e.g., *I understand my child's needs*), and– emotion and affection (six items; e.g., *I am able to show affection to my child*)six items from the parenting questionnaire used in the Longitudinal Study of Australian Children (LSAC) (50), exploring:
– hostile parenting (five items; e.g., *When this child cries, he/she gets on my nerves*) scored on a 10-point scale– parent overall rating of child difficultness (from the Australian Temperament Project (51)); single item; *Compared to the average child, do you think your child is…*) scored on a 5-point scale, ranging from *Much less difficult* to *Much more difficult*seven items from the Caregiving Helplessness Questionnaire (Mother Helpless subscale, CHQ (52)); e.g., *When I am with my child, I often feel out of control*) scored on a 5-point scalethe full 18-item Diamond Maternal Reflective Functioning Scale [DMRFS; (53); e.g., *I think about what my child may be thinking or feeling*] scored on a 4-point scale

Preliminary reliability and validity assessments for the subscales, as combined in the CCQ, were undertaken on a pilot sample of 81 parents. Internal consistency was very good; Chronbach's alpha coefficients ranged from 0.78 (TOPSE emotion and affection) to 0.88 (TOPSE empathy and understanding, and LSAC hostility). Associations among subscales (plus depression symptoms) aligned with theoretical expectations, but they were moderate, confirming that the different subscales captured different aspects of parenting: e.g., hostility was positively correlated with caregiving helplessness (0.68) and depression symptoms (0.54) and negatively correlated with empathy and understanding (−0.34); caregiving helplessness was negatively correlated with empathy and understanding (−0.57); and positively correlated with depression symptoms (0.57). Self-reported caregiving representations and parental mentalization will be compared with assessments of these outcomes using validated interview and observational measures during this study, as part of the ongoing CCQ validation process.

##### The circle of security interview

Augmenting the CCQ, the Circle of Security Interview [COSI; (9)] will enable a more in-depth assessment of caregiving representations. The COSI is based on two widely validated instruments to assess attachment and caregiving representations, respectively, the Adult Attachment Interview (AAI) (54); and the Parent Development Interview (PDI) (55). The COSI forms part of the 20-week COS-I treatment protocol, and differs from the two source measures by including direct questions to the parent about their experience of the Strange Situation Procedure (SSP). The final question asks the caregiver what they hope the target child learns from being parented by them. Like the AAI and the PDI, the COSI is a narrative interview, designed to “surprise the unconscious” [(54), p. 19], and is thus less prone to response bias than a questionnaire.

In the current study, the questions related to the SSP will be omitted. Interviews will be audio recorded and transcribed, and de-identified transcripts will be used for coding. Responses to the questions exploring perceptions of self in the caregiving role and relationship with the target child will be coded using a coding system developed by [name] and colleagues (16). This eight-scale system comprises two affect dimensions, reflecting the caregiver's feelings about the child and/or their relationship, and six dimensions reflecting the caregiver's self-perception in the caregiving role (16). The system shows promising validity, with theoretically expected associations between one subscale (“weak”) and observed dimensions of attachment (negatively correlated with attachment security and positively with attachment disorganization) (16) and between the total representations score and parental mentalizing (positive correlation with appropriate mind-related comments) (56).

##### Interview and observational assessments of caregiver mind-mindedness

To supplement the CCQ, more in-depth measures of parental mentalization will be included. The mind-mindedness interview question (*Please describe your child*) (57) will be added to the COSI. Parent spontaneous descriptions of their child, together with parent language during the 5-min videotaped caregiver-child interaction, will be transcribed and coded, respectively, for representational and observational mind-mindedness (58, 59), according to Meins and Fernyhough's coding manual (57). Mind-mindedness is a measure of parental mentalization specific to the child (60), and one of the most feasible and cost-effective to administer and code (61). Mind-mindedness has shown consistent associations with parental sensitivity and child attachment (61).

#### Secondary Outcomes

The two secondary study outcomes are caregiver-child interaction quality, assessed from observed caregiver-child interaction, and caregiver depression symptoms (also being tested as a moderator), assessed through a self-report questionnaire.

##### Caregiver-child interaction coding scheme

Caregiver-child interaction videos will be coded using an adaptation of the coding scheme for assessing maternal interactive style developed by Calkins and colleagues (62) and validated for short interactions by Bernier and colleagues (63). The two original versions of the scheme (one for mothers of 5- and 10-month-old infants, and one for mothers of 24-, 36-, and 48-month-old children) were combined to form a single coding scheme suitable for use with children from infancy to 5 years of age, including guidance on developmental variations. The adapted coding scheme comprises four scales for rating caregiver behavior and one scale for rating child behavior. Three of the caregiver scales were part of in the original measures—sensitivity (previously called Facilitates Attention), Intrusiveness, and Hostility (previously called Negative Affect). An additional caregiver scale, Autonomy Support, based on work by Whipple and colleagues (64), and one child scale, Child Inclusion of Caregiver, have been added. Following the approach used by Calkins and colleagues (62) each 5-min video will be coded in ten 30-s intervals. Ratings for each scale will be summed across the 10 intervals and then divided by 10 to give a mean value. Following initial adaptation, the new coding scheme will be refined during group coding of the first 10 video cases by the three study coders.

##### Edinburgh postnatal depression scale (EPDS)

The EPDS (65), already in routine use at three of the four study sites, will be used to assess depression symptoms before and after the group. This well-validated measure comprises 10 questions exploring possible symptoms of depression, designed to be suitable for use in the postnatal period as few items refer to maternal sleep and appetite disturbances which are to be expected with a newborn. Although the EPDS was developed to screen for depression in antenatal and postnatal women, it has been validated for the assessment of mothers of preschool-aged children (66), fathers (67), and adults in the general population (68). While depression symptoms are not an explicit primary or secondary target of COS-P, there is some evidence from the limited COS-P research to date that depression symptoms are improved following COS-P (24, 69), and maternal depression is commonly examined as a moderator of the effectiveness of attachment-based interventions (26).

#### Monitoring Intervention Fidelity

##### COS-P fidelity interview

A brief structured interview was developed to track program fidelity during this study. Questions administered to all COS-P facilitators at the end of each group will probe adherence to the COS-P manual and DVD clips. Any content excluded or added will be noted. This interview will also provide an opportunity for facilitators to share any factors they noted during the group that might influence intervention completion or outcomes for specific participants, e.g., divorce, separation, or death of a significant other during the course of the group, presence of a partner in the group, etc.

#### Ensuring Caregiver and Child Safety

As all study participants will be clients of a clinical service, they will be allocated to a case manager or clinician at that service, and their mental health and well-being will be routinely monitored. Potential study participants will be excluded from the group (and therefore, the study) by clinical staff if they are too impaired due to severe mental illness, suicidality, or psychosis, and referred for more intensive support. Given different service types and resource levels, some services provide this internally, while others will refer externally. In addition to routine monitoring, Time 1 and Time 2 EPDS assessments will be used to detect mental health symptom severity and risk. Study sites have established protocols and pathways for parents that score in the likely-to-be-depressed range (>12) or endorse item 10 (risk item). In addition, during COS-P group participation, clinicians routinely assess and monitor for mental health symptoms, risk to children, and domestic violence, with site-specific protocols in place. In addition to established site protocols for ensuring caregiver and child safety, there will be regular communication between the research team and clinical and managerial staff at the study sites. At clinical service discretion, parents with significant risk or safety issues, and/or who require more intensive, individual interventions, will be withdrawn from the study and referred as above.

### Sample Size Calculation

Power analyses were conducted using G^*^Power 3.1 (70). Based on preliminary CCQ data for the first 67 intervention group participants, a total sample size of 128 was indicated to detect a medium intervention effect with 80% power and an error level of 0.005 (for multiple comparisons). Assuming an attrition rate of 20%, we aim to recruit a total of 154 participants to complete study questionnaires. Sample size for the interview and observational study measures was calculated based on analysis of data from the COSI interview in a previous comparable study (16). While there was a large intervention effect on caregiving representations in that study, it is estimated the effect size will be smaller in the current study given the shorter duration and lower intensity of the intervention. To detect a medium effect size with 95% power and an error level of 0.05, assuming a Time 1–Time 2 correlation of 0.5, a sample size of 40 was indicated. Assuming an attrition rate of 20%, we aim to include a subsample of 48 participants completing interview and observational study measures (COSI and/or videotaped caregiver-child interaction) in addition to questionnaires.

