**Figure 1 F1:**
[figure not shown]
Circle of Security circle graphic. Copyright 2016 by Cooper, Hoffman, and Powell. Reproduced with permission.

COS-P is broadly disseminated in North America, Europe, and Asia, and has proved particularly popular in Australia, where more than 10,000 COS-P facilitators had been trained by late 2016 (14). This figure will now be substantially higher, with more than 10 official COS-P training courses held around the country each year, often training more than 200 individuals at a time. Several state government departments and large non-profit organizations have adopted COS-P and/or the overarching COS model to inform their work with families of young children. Surprisingly, however, evidence for COS has not kept pace with dissemination (5), with remarkably few evaluation studies published to date for either version, precluding their endorsement as evidence-based programs by bodies like the influential California Evidence-Based Clearinghouse for Child Welfare (15).

Two studies of the intensive COS-I intervention with pre-post-designs have shown improvement in indices of child attachment in U.S. (13) and Australian (16) samples. The second of these studies also showed an increase in caregiver reflective functioning and caregivers' positive caregiving representations (16), improvements in child behavior problems and child social-emotional protective factors (17), and reductions in parenting stress and parent mental health symptoms (18). While these results are encouraging and in line with theory, they are limited by the absence of a control condition, small sample size, and the study context (single clinical setting).

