To date, there are eight published studies evaluating the effectiveness of COS-P for parents. Five had very small samples (ns from 1 to 15). None of these included control or comparison groups and all but one used only self-report questionnaires to measure outcomes. Two were single case studies, the first of which showed post-COS-P improvements in parenting stress, perceptions of self-agency and child functioning, and parenting alliance (19). The second case study showed a reduction in attachment insecurity, anxiety and depression symptoms, and perceptions of child internalizing and externalizing behavior problems following COS-P (20). Two other studies (both *n* = 15) showed post-COS-P improvements in parents' self-reported emotion regulation, attributions about the child's behavior and discipline practices (21), and decreases in caregiver helplessness, feelings of fear, anger, and rejection toward the child, and levels of maternal stress (22). One study with a sample of opiate-dependent caregivers of young children (*n* = 8), reported a post-COS-P reduction in caregiver substance use and in depression, anxiety, and stress symptoms (23).

Three larger COS-P evaluation studies have been published recently. One was a multi-site evaluation of community delivery of COS-P (with no control or comparison group; *n* = 131), which focused primarily on the challenges of program delivery in a low socio-economic area in urban Connecticut, USA (24). Maupin and colleagues reported a reduction in caregiver depressive symptoms following COS-P, with a medium effect size, but no changes in caregiver reports of competency, reflective functioning, and the parent-child relationship. Significant implementation challenges were noted, including limited access to the resources needed to run groups (venue, printing facilities, computer equipment), failure to integrate COS-P into clinical caseloads, and limited clinical supervision.

Risholm Mothander and colleagues (25) reported results of a randomized trial (*n* = 52) examining COS-P plus treatment as usual (TAU), compared with TAU alone, in three Swedish infant mental health clinics. Parents in the COS-P group showed significant increases in balanced caregiving representations (interview measure) and in emotional availability (observational measure) 12 months after baseline. There was no significant change in outcome for the TAU-only group in the same period. However, differences between the two groups were not significant.

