### The Current Study

The primary aim of the current study is to examine the effectiveness of COS-P for caregivers who present to early parenting support services with parenting concerns, often in the context of PND. Study outcomes have been selected with reference to a recently developed theory of change for COS-P (46), which proposes that COS-P works to improve aspects of caregiving that may be necessary prerequisites for secure attachment, including caregiving representations (i.e., how the caregiver thinks and feels about the child, themselves as a caregiver, and their relationship with the child) and child-focused mentalization (the ability to be aware of and make inferences about mental states of self and child, and their impact on behavior). These components of relational caregiving capacity are theorized primary outcomes of COS-P. Changes in parent behavior, and in child attachment and/or behavior are not directly targeted by the intervention, but may be longer-term outcomes of targeted improvements in caregiving, and thus are considered secondary outcomes (46).

We aim to establish if COS-P is effective in building caregiving capacity through an increase in (a) positive representations of the child and self as caregiver, (b) more accurate caregiver mentalization, (c) more responsive caregiving behavior, and (d) reduction of caregiver depression symptoms. We hypothesize that caregivers receiving COS-P will show greater improvements in these areas than caregivers in a waitlist condition.

Given that COS-P research to date includes disparate (and often small) samples with a range of risk factors, we also intend to examine whether socio-demographic (e.g., caregiver language background, gender, education level, child age) and psychosocial (e.g., severity of depression symptoms) risk factors moderate response to the intervention, to extend knowledge of what works for whom. Due to limited empirical data available on COS-P outcomes, we do not posit directional hypotheses regarding the moderating effects of examined demographic and psychosocial risk factors.

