## Methods and Analysis

### Design

This study is a multi-site non-randomized controlled effectiveness study of COS-P, with treatment and waitlist control group participants undergoing assessment at two time points. The multi-site design both reflects the broad dissemination of COS-P and enables recruitment of sufficient participants to meet sample size requirements (see power analysis, below). The study design was determined in consultation with the study sites (see study setting, below); senior managerial staff indicated willingness to support incorporation of the study into their service, but maintained that they could not accommodate a randomized trial. Thus, participant allocation to treatment and waitlist control conditions will not be randomized, but dependent on the scheduled timing of the COS-P group in which they are enrolled. At study entry, participants whose COS-P group will commence within 7 weeks will be allocated to the treatment group. Participants whose COS-P group will commence eight or more weeks hence will be offered a place in the waitlist control group. Circumstances that may contribute to the latter include a long COS-P waiting list at the study site, registering just after a COS-P group has been filled or has started, inability to attend the next available group due to scheduling clashes, being assigned to a group that is subsequently canceled due to insufficient numbers, and the long gap between groups over the summer shutdown period. However, both treatment and control group participants must be determined to be “COS-P-ready” according to standard clinical procedure prior to their participation in the study. Waitlist control group participants will be free to engage with other forms of treatment or support within and outside of the organization prior to commencing the group. This study has been approved by the relevant university, health department and service-specific ethics committees (Macquarie University Human Research Ethics Committee: 5201600788; St John of God Healthcare Human Research Ethics Committee: 1153; Sydney Local Health District Ethics Review Committee: HREC/17/RPAH/285 & SSA/17/RPAH/432; ACT Health Human Research Ethics Committee: ETH.9.17.221E).

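### The medium effect behind both sample sizes is supported only by uncontrolled data, with no allowance for change in the waitlist; the subsample of 40 does not give 95% power for a medium between-arm difference in change

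*Protocol article*

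**What the plan says.** The Current Study section sets a between-arm hypothesis: "We hypothesize that caregivers receiving COS-P will show greater improvements in these areas than caregivers in a waitlist condition". Data Analysis plans a mixed design ANOVA on two groups at two time points.

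The Sample Size Calculation section gives two sizes.

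- **Questionnaires.** "Based on preliminary CCQ data for the first 67 intervention group participants, a total sample size of 128 was indicated to detect a medium intervention" (an unquantified effect). The stated power is 80% and the error level 0.005. No control data are mentioned, and the section does not say what was taken from the 67 participants.
- **Interview and observation subsample.** A size of 40 is given for a medium effect, 95% power, an error level of 0.05 and a Time 1–Time 2 correlation of 0.5. The source is interview data from an earlier study of the 20-week intervention, which had a large effect. The reduction to medium is explained in these words: "it is estimated the effect size will be smaller in the current study given the shorter duration and lower intensity of the intervention".

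The Introduction classes that earlier study among two with pre-post designs and says of their results that "they are limited by the absence of a control condition, small sample size, and the study context (single clinical setting"). The Design section adds: "Waitlist control group participants will be free to engage with other forms of treatment or support within and outside of the organization". The Discussion accepts that elements of the model may reach the care given to the waitlist. No section puts a figure on waitlist change.

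**The concern.** A before-after change in treated caregivers equals the effect against a waitlist only if the waitlist does not change. In help-seeking parents, such a change can also contain natural recovery, regression to the mean and the effect of other care. The control arm here is exposed to all three. The large effect from the earlier study is lowered for duration and intensity, but not for control change.

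The article itself reports that the two contrasts can part. In the Swedish trial (n = 52) the COS-P arm improved significantly. "However, differences between the two groups were not significant".

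At stake is how a null result is read. Stated power of 80% or 95% invites the conclusion that a medium benefit over waitlist has been ruled out. If the study could detect only a much larger net difference, that conclusion would be wrong.

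**Working it through.** **Inputs from the article:** total 128, 80% power, alpha 0.005; total 40, 95% power, alpha 0.05, r = 0.5.

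**Assumptions, not in the article:** equal arms, two-sided tests, and medium read as d = 0.5 or f = 0.25. For the questionnaires, r = 0.5 is also assumed.

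**Scale.** SD of change = SD × √(2(1 − r)). At r = 0.5 this is SD × √1, so the SD of change equals the SD of the measure.

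**Test.** Two-sample t on change scores, n per arm, net difference d in SD of change: noncentrality = d × √(n/2), with 2n − 2 degrees of freedom.

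**1. Reproducing 128.**
- n = 64, d = 0.5: noncentrality = 0.5 × √32 = 2.83. Power is 80% at alpha 0.05 and 49% at alpha 0.005.
- 128 is exactly the smallest total for this two-arm test at alpha 0.05. At alpha 0.005 it would be 218.
- A paired one-arm calculation with a standardised change of 0.5 needs 58 at alpha 0.005 and 34 at 0.05. Group-by-time with f = 0.25 and r = 0.5 also needs 58 at 0.005. None of these gives 128.

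**2. Reproducing 40.**
- Two-arm t on change, n = 20, d = 0.5: noncentrality = 0.5 × √10 = 1.58; power 34%.
- Group-by-time interaction with f = 0.25, two measurements: λ = f² × N × 2 / (1 − r) = 0.0625 × 40 × 2 / 0.5 = 10; power 87%. For 95% the total needed is 54.
- The difference in change implied by that f: D² × 10 = 10, so D = 1.0 SD.
- Paired one-arm, 40 participants, standardised change 0.5: power 87% two-sided, 93% one-sided.
- No reading tried gives 95% at 40 with a conventional medium effect. The interaction reaches it at f of about 0.30.

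**3. Net difference each size can detect** (two-sided t on change, equal arms):

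| Total | Alpha | Power | Detectable net difference |
|---|---|---|---|
| 128 | 0.05 | 80% | about 0.50 SD |
| 128 | 0.005 | 80% | about 0.66 SD |
| 40 | 0.05 | 95% | about 1.17 SD |
| 40 | 0.05 | 80% | about 0.91 SD |

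**4. Sensitivity to waitlist change.** If the treated arm changes by 0.5 SD and the waitlist by w, the net difference is 0.5 − w. Both figures are assumptions; the article gives neither.

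| w | Net | 128, alpha 0.05 | 128, alpha 0.005 | 40, alpha 0.05 |
|---|---|---|---|---|
| 0 | 0.5 | 80% | 49% | 34% |
| 0.1 | 0.4 | 61% | 28% | 23% |
| 0.2 | 0.3 | 39% | 13% | 15% |
| 0.3 | 0.2 | 20% | 4.5% | 9.5% |

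The first row is low at alpha 0.005 and for 40 before any waitlist change. Those shortfalls come from the error level and the effect metric. Only the fall down each column is due to waitlist change.

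**The case against.** A reader might infer that both sizes were computed from a one-arm before-after effect, so that neither stated power applies to the comparison the study makes. The documents do not support that.

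- The article does not say that a before-after effect was taken from the 67 participants. An SD or a correlation may be all that was used. The arithmetic in fact points to a two-arm calculation for 128.
- Both power statements are conditional on a medium effect. Read as a net between-arm effect, that is a legitimate target whatever the waitlist does.
- It does not follow that the net effect is below medium. The treated change on the questionnaire is not reported, and the one observed effect mentioned was large. A treated change above 0.5 SD could still leave a medium net effect.
- The Swedish trial was small, so its non-significant difference does not show a small effect. The largest trial reported small to medium effects, a range that includes medium.
- The Discussion recognises blurring between the arms and promises to consider it in interpretation. No section says that a null result will be read as absence of effect.

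All of this stands, and it limits the questionnaire point to an effect assumption without controlled support. It does not rescue the subsample, where 95% is not reached on the two-arm, the interaction or the paired reading. Nor does it supply the missing contrast, test and metric: once a section states its inputs and its power, the reader needs to know which difference they refer to.

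**Conclusion.** The concern holds in limited form. The article supports its medium effect only with treated participants and an uncontrolled study, while the hypothesis is a difference in improvement from a waitlist free to seek other help. No allowance is made for waitlist change.

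For the questionnaires this is an unsupported assumption, not a demonstrated use of the wrong contrast. That 128 fits alpha 0.05 and not the stated 0.005 is a separate fault, and correcting it would leave this one in place.

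For the subsample the stated figure itself fails: power is 34% for a 0.5 SD between-arm difference in change, or 87% if medium means a 1.0 SD difference, against the 95% claimed. These results rest on equal arms, two-sided tests, r = 0.5 and conventional values for medium. The waitlist range of 0 to 0.3 SD is illustrative and not an estimate.

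**What to change.** In the Sample Size Calculation section:

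1. Define the sizing effect as the net between-arm difference in Time 1–Time 2 change, and name the test and the effect metric.
2. Say that the 67-participant data and the earlier study are uncontrolled, and use them only for the SD and the Time 1–Time 2 correlation.
3. Replace the two power claims with the detectable net differences tabulated in the working, with their assumptions.
4. Optionally, show power across an assumed waitlist improvement of 0 to 0.3 SD as a sensitivity range.
5. State that non-significant results will be interpreted by the confidence interval for the between-arm difference, not by the planned power.

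The cost is a short recalculation and a rewritten paragraph. Recruitment and the main analysis do not change, but the stated power becomes less favourable.

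### The stated inputs do not reproduce 128 participants for 80% power at an error level of 0.005; with d = 0.5 assumed, 128 is exactly the requirement at 0.05

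*Protocol article*

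**What the plan says.** The Sample Size Calculation section links four quantities for the questionnaire outcomes: "a total sample size of 128 was indicated to detect a medium intervention effect with 80% power and an error level of 0.005". The error level is marked there as an allowance for multiple comparisons. The section gives the basis as "Based on preliminary CCQ data for the first 67 intervention group participants" and names G*Power 3.1 as the software. It reports no numeric effect size, standard deviation, test family, sidedness or correlation for this calculation.

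The same paragraph makes a second calculation for the interview and observation subsample: medium effect, 95% power, error level 0.05, correlation 0.5 between the two time points, and 40 participants. That correlation is the only one of its kind in the article. The Data Analysis section plans a mixed design ANOVA on two groups measured twice.

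**The concern.** A total of 128 is the familiar answer for a two-group comparison at d = 0.5, 80% power and two-sided 0.05. Here it stands beside an error level ten times stricter, which the article says is there for multiple comparisons. A stricter level with effect and power unchanged must raise the number needed, so the four quantities cannot all belong to that calculation.

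The figure carries weight. The Procedure section gives the questionnaires to every participant and the interview and video only to a subsample. Of the two questionnaires, the Composite Caregiving Questionnaire (CCQ) carries primary outcomes and the depression scale is secondary. The CCQ is therefore the only primary measure with full-sample data, and this paragraph is the only statement of what that sample can detect. If the true power at 0.005 is well below 80%, a non-significant CCQ result says much less against a medium effect than a reader of the paragraph would suppose.

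**Working it through.** **Inputs.** From Sample Size Calculation: total N = 128, power 80%, error level 0.005, medium effect. Assumed, because not stated: d = 0.5 (equivalently f = 0.25 for two groups), two-sided test, 64 per group.

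**Formula.** For a two-sample t-test with n per group, the noncentrality is d × √(n/2) on 2n − 2 degrees of freedom. Power is the probability that the noncentral t exceeds the two-sided critical value.

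**Step 1: reproduce 128.** With n = 64, the noncentrality is 0.5 × √32 = 2.828 on 126 df.
- At 0.05 the critical value is 1.979 and power is 80.1%. With 63 per group it is 79.5%, so 64 per group (128) is the exact minimum.
- At 0.005 the critical value is 2.857, just above the noncentrality, and power is 49.1%.

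**Step 2: number needed at 0.005.** 108 per group gives 79.8% and 109 per group gives 80.2%, so the total is 218. Analysing all 154 planned recruits with no loss would give 60.1%. A one-sided test at 0.005 needs 192 and has 58.5% power at 128.

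**Step 3: use the repeated measurement.** Let ρ be the correlation between Time 1 and Time 2. The effective standardised effect is d / √(2(1 − ρ)) for change scores and d / √(1 − ρ²) with baseline adjustment. Power at N = 128 and 0.005:

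| ρ | Change score | Baseline-adjusted |
|---|---|---|
| 0.5 | 49% | 66% |
| 0.6 | 62% | 75% |
| 0.65 | 70% | 80% |
| 0.7 | 78% | 86% |
| 0.71 | 80% | 87% |

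At ρ = 0.5 the numbers needed are 218 and 164. About 80% at N = 128 needs ρ of about 0.71 or 0.65 respectively.

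**Step 4: other routes in the named software, at 0.005 and 80% power.**
- Within-between interaction, f = 0.25: noncentrality f² × N × 2 / (1 − ρ). N is 58 at ρ = 0.5, 80 at ρ = 0.3 and 112 at ρ = 0. No non-negative correlation gives 128.
- Between-groups factor, f = 0.25, ρ = 0.5: N = 164.
- ANCOVA with two covariates, f = 0.25: N = 218. At 0.05 it needs exactly 128.
- Repeated-measures ANOVA with the effect size specified as in Cohen, f = 0.25: N = 218. At 0.05 it needs exactly 128.

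**Step 5: effect detectable at N = 128.** With no gain from correlation, 80% power at 0.005 needs d = 0.655, about 0.66.

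Three standard routes (t-test, ANCOVA and the Cohen option) return exactly 128 at 0.05. None returns it at 0.005 from anything the article states.

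**The case against.** The best defence is that the calculation is said to rest on preliminary CCQ data from 67 participants. Pre-post data of that kind could supply a correlation. The pilot internal consistencies of 0.78 to 0.88 leave room for a correlation of 0.65 to 0.71 over 7 to 11 weeks, and with such a value 128 would give about 80% at 0.005. A journal article may also condense its inputs. This stands: 49% is conditional on assumptions, and a reader should not infer from the article that the trial's power is known to be 49% or that a mix-up is established. It does not rescue the paragraph as written, because the unreported inputs would have to land by chance on the textbook figure for 0.05.

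Two further points are fair. The correlation of 0.5 was stated for the interview subsample, not the CCQ, so the 49% and 66% in Step 3 borrow it. Also, the subsample figure of 40 is not reproduced at f = 0.25 and ρ = 0.5 (the interaction route needs 54), so medium may not mean the textbook value in this paragraph. Both are reasons to state the effect and correlation, not evidence that 128 is right.

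A reader might also infer that allocation by group timing, with 67 already in the intervention arm, damages power further. The article does not support this. It states no allocation ratio, and a 67:61 split still gives 80.1% at 0.05 and 49.0% at 0.005.

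**Conclusion.** The point holds in conditional form. As written, the pairing of 128 with 80% power at 0.005 cannot be obtained from any input in the article. Under d = 0.5, a two-sided test and equal groups, power at 0.005 is about 49% rather than 80%, and 218 analysed participants would be needed rather than 128. With a correlation of 0.5 and baseline adjustment, power is 66%, still short of the claim.

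That a corrected error level was joined to an uncorrected sample size is the likeliest explanation, because 128 matches the 0.05 requirement exactly. It remains an inference. The fault lies in the power statement; it does not bias the estimated effect.

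**What to change.** Restate the paragraph in one of three ways.

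- **Keep 0.005** and give the power that 128 analysed participants provide: about 49% for d = 0.5 with no gain from correlation, and 80% only for d of about 0.66.
- **Correct the error level for the 128 to 0.05** and say how multiplicity across the CCQ outcomes will be controlled. The choice of procedure is the authors'.
- **If the preliminary CCQ data gave a correlation or effect that yields 128 at 0.005**, report that value, the definition of the effect (difference at Time 2, in change, or baseline-adjusted) and the test used.

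The cost is one paragraph of rewording and no added recruitment. Under the first option the stated power becomes less favourable; under the second, the multiplicity adjustment needs its own sentence.
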